## Statistical analysis methods

### General principles and descriptive statistics

All statistical analyses will employ two-sided tests with a significance threshold of α = 0.05, and results will be reported with 95% confidence intervals. Bonferroni correction or false discovery rate (FDR) adjustment will be applied to control Type I error inflation in the context of multiple comparisons. Multivariable regression models will be constructed within the competing-risk framework to identify independent prognostic predictors of consciousness recovery, as detailed in the Primary Analysis subsection below. Separately, a dedicated multimodal prognostic prediction model will be developed and validated using a three-stage hierarchically nested approach incorporating LASSO-based variable selection and bootstrap internal validation (1,000 resampling iterations); the C-index will serve as the primary discrimination metric. The full construction procedure for this prediction model is described in the dedicated subsection below.

### Primary analysis

For the primary outcome of consciousness recovery, a competing-risk analytical framework will be applied, in which consciousness recovery is designated as the event of interest and all-cause mortality as the competing risk event. Cumulative Incidence Functions (CIFs) will be estimated, and the Fine-Gray subdistribution hazard model will be used to assess the influence of each predictor on the subdistribution hazard of recovery. For the single-endpoint outcome of all-cause mortality, Cox proportional hazards regression will be employed. Covariates will be introduced in a stepwise fashion across five models: Model 1 (unadjusted); Model 2 (adjusted for demographic variables: age and sex); Model 3 (Model 2 plus clinically relevant injury-related variables: etiology [TBI vs. HIE vs. cerebrovascular vs. metabolic/toxic encephalopathy vs. other], GCS at acute admission, and time from injury to enrollment); Model 4 (Model 3 plus baseline CRS-R total score and neuroimaging indices [DTI-FA and fMRI-DMN connectivity]); and Model 5 (fully adjusted model incorporating all prespecified covariates: age, sex, educational level, comorbidities, etiology of brain injury, GCS at acute admission, time from injury to enrollment, baseline CRS-R total score, and neuroimaging indices). Covariate selection will be guided by directed acyclic graph (DAG) construction and prior literature evidence to avoid bias introduced by over-adjustment of mediators and colliders.

The proportional hazards assumption will be tested using Schoenfeld residuals and log–log survival plots; violations will be addressed through stratified Cox models, time-varying covariates, or restricted cubic splines. Results will be expressed as hazard ratios with 95% confidence intervals. Kaplan–Meier curves will be used to visualize survival probabilities across exposure groups, and forest plots will be employed to display effect estimates and their trends across adjusted models.

In addition to the primary time-to-event analysis, a pre-specified nested prognostic comparison will be conducted between participants who achieve the consciousness recovery endpoint and those who do not (either remaining in VS/MCS or experiencing death as a competing event), using the Fine-Gray subdistribution hazard model incorporating all primary prognostic predictor variables (etiology, GCS at acute admission, time from injury to enrollment, CRS-R subscale scores at baseline, and neuroimaging indices). This nested comparison is designed to identify the multivariate prognostic profile that discriminates recovery-positive from recovery-negative trajectories within the cohort.

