### Study objectives

This study aims to systematically characterize the 5-year natural history of pDoC through a prospective cohort design, thereby bridging the critical evidence gap stemming from the absence of large-scale, long-term follow-up investigations. The specific objectives are as follows:To determine the rates of consciousness recovery, all-cause mortality, and major cardiovascular events over a 5-year follow-up period in patients stratified by initial level of consciousness (VS, MCS−, and MCS+); primary comparisons will be conducted at the VS vs. MCS level, with MCS − vs. MCS + differentiation examined in prespecified subgroup analyses.To identify etiology, injury severity (GCS at admission), time from injury to enrollment, Coma Recovery Scale–Revised (CRS-R) subscale profiles, and neuroimaging indices as independent predictors of consciousness recovery and unfavorable outcomes.To develop and validate a multimodal prognostic prediction model integrating clinical, neuroimaging, and biomarker data.

The primary research question of this study is: among patients with prolonged disorders of consciousness (VS or MCS ≥ 28 days post-acute brain injury), does baseline consciousness level (VS vs. MCS) independently predict 5-year consciousness recovery trajectory, after adjustment for etiology, injury severity, and neuroimaging characteristics?

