### Study population

The target population comprises individuals currently diagnosed with pDoC—specifically VS or MCS (encompassing both MCS − and MCS+)—at the time of enrollment. Patients who have already achieved eMCS prior to enrollment are not eligible, as eMCS constitutes the primary consciousness recovery endpoint of this study. Patients with post-traumatic confusional state (PTCS), which represents a transitional state beyond eMCS in the TBI recovery trajectory, are likewise not eligible for enrollment. Both conditions are characterized by persistent alterations in consciousness following severe acquired brain injury: VS is defined by wakefulness without awareness, whereas MCS indicates the preservation of partial conscious awareness.

Inclusion criteria are as follows: (1) a confirmed diagnosis of DoC with a duration of at least 28 days, established according to the 2020 European Academy of Neurology (EAN) guidelines (6) and assessed using the validated Chinese version of the CRS-R (7), including vegetative state (VS) and minimally conscious state (MCS; encompassing both MCS − and MCS+); (2) age between 18 and 80 years; (3) provision of written informed consent by the participant (if possessing decision-making capacity) or by a legally authorized representative (LAR); and (4) availability of complete medical records documenting the etiology of the initial brain injury, injury severity, and relevant diagnostic investigations. Eligible etiologies include all forms of acquired brain injury that can lead to prolonged disorders of consciousness (pDoC), such as traumatic brain injury (including both closed and penetrating head injuries) and non-traumatic brain injury—including hypoxic-anoxic injury (e.g., due to cardiac arrest, respiratory failure, or near-drowning), cerebrovascular events (such as ischemic stroke, hemorrhagic stroke, and subarachnoid hemorrhage), and metabolic or toxic encephalopathies.

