#### Exposure variable

The primary exposure variable is the baseline level of consciousness (VS or MCS) at enrollment. All enrolled participants will receive standardized multimodal rehabilitation care in accordance with the Chinese Expert Consensus on the Diagnosis and Treatment of Prolonged Disorders of Consciousness (Standard of Care, SOC) (10), encompassing: (1) pharmacological arousal-promoting therapy (e.g., amantadine, donepezil, zolpidem); (2) multimodal sensory stimulation therapy (auditory, tactile, visual, and olfactory modalities); (3) physical therapy (including tilt-table training and passive mobilization); (4) occupational therapy; (5) speech-language therapy; (6) hyperbaric oxygen therapy (where indicated and available); and (7) neuromodulation techniques (e.g., median nerve electrical stimulation, repetitive transcranial magnetic stimulation, spinal cord stimulation), as well as evidence-based complication management (infections, spasticity, pressure injury). Treatment intensity for each modality will be quantified as total weekly contact time (minutes per week) and session frequency, recorded prospectively in the electronic data capture system at each assessment timepoint. All treatment variables will be incorporated as time-dependent covariates (operationalized as weekly contact time (min/week) per rehabilitation modality) in the analytical models to distinguish the natural disease course from treatment-mediated effects.

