### Subgroup and interaction analyses

Prespecified subgroup analyses will be conducted based on clinical relevance and potential effect modification, including: age (< 50 years vs. ≥ 50 years), sex (male vs. female), injury type (traumatic vs. non-traumatic), and baseline level of consciousness (VS vs. MCS). Interaction terms (product terms between the exposure variable and subgroup variables) will be introduced into multivariable regression models to formally test the statistical significance of interactions, with a significance threshold of *p* < 0.10. Statistically significant interactions will be further examined through stratified subgroup analyses, with results displayed as forest plots showing HRs and 95% CIs for each subgroup. All subgroup analyses will be characterized as exploratory findings to prevent overinterpretation.

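### No listed model estimates the VS vs MCS effect with neuroimaging but without baseline CRS-R total, and the exposure is listed as its own interaction factor

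*Protocol article*

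**What the plan says.** Study objectives puts the primary question as follows: "does baseline consciousness level (VS vs. MCS) independently predict 5-year consciousness recovery trajectory, after adjustment for etiology, injury severity, and neuroimaging characteristics". Exposure variable states: "The primary exposure variable is the baseline level of consciousness (VS or MCS) at enrollment". Under Study population, the diagnosis follows the 2020 EAN guideline and is "assessed using the validated Chinese version of the CRS-R".

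Primary analysis builds five models in steps. Model 3 has age, sex, etiology, GCS at acute admission and time from injury. The next step is "Model 4 (Model 3 plus baseline CRS-R total score and neuroimaging indices [DTI-FA and fMRI-DMN connectivity". Model 5 adds educational level and comorbidities and keeps both the CRS-R total and the imaging indices. The same paragraph says that a DAG and prior literature will guide covariate selection, so as to avoid over-adjustment.

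Subgroup and interaction analyses ends its list of factors with "injury type (traumatic vs. non-traumatic), and baseline level of consciousness (VS vs. MCS" and defines the tests as "Interaction terms (product terms between the exposure variable and subgroup variables".

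**The concern.** VS/MCS and the CRS-R total come from the same instrument at the same baseline. With both in one model, the VS/MCS coefficient no longer compares patients at different levels of consciousness. It compares patients with the same total score who carry different labels, and so measures what the label adds beyond the score. The primary question does not ask that.

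A reader who takes the fully adjusted model as the answer could conclude that baseline consciousness level has little independent value, when the model has already conditioned on a close measure of it.

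The subgroup list has a separate fault. Its interaction terms are products with the exposure, and one factor on the list is the exposure.

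**Working it through.** **Step 1. Adjustment sets side by side.** Injury severity is GCS at admission (Study objectives).

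| | Etiology | GCS | Neuroimaging | CRS-R total |
|---|---|---|---|---|
| Primary question | yes | yes | yes | no |
| Models 1-2 | no | no | no | no |
| Model 3 | yes | yes | no | no |
| Model 4 | yes | yes | yes | yes |
| Model 5 | yes | yes | yes | yes |

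Age, sex, education, comorbidities and time from injury are ordinary additions and not at issue. Neuroimaging and CRS-R total enter in one step, so no row matches the primary question. CRS-R total is also absent from the adjustment covariates in Predictor variables and covariates (age, sex, education, comorbidities); that section lists CRS-R subscales as predictors. This step needs no assumption beyond reading VS/MCS as the term of interest in the five models.

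**Step 2. The plan's own figure.** Inputs from Sample size calculation: HR 1.3, two-sided α 0.05, power 80%, exposure proportion 0.3. Schoenfeld:

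D = (1.960 + 0.842)² / [0.3 × 0.7 × (ln 1.3)²] = 7.849 / (0.21 × 0.06884) = 542.97, so 543 against the stated 544. The figure reproduces. The formula has no allowance for covariates correlated with the exposure.

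**Step 3. Precision lost by adding a correlated covariate.** Let R² be the share of variance in the VS/MCS label explained by the other covariates. The effective number of events is D(1 − R²), and

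power = Φ(√[D(1 − R²) × 0.21] × 0.2624 − 1.96).

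With D = 544:

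- R² 0: √114.24 × 0.2624 − 1.96 = 0.844, power 80%.
- R² 0.25: √85.68 × 0.2624 − 1.96 = 0.469, power 68%.
- R² 0.5: √57.12 × 0.2624 − 1.96 = 0.023, power 51%.

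Events needed to restore 80%: 542.97/0.75 = 724 and 542.97/0.5 = 1,086.

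R² is an assumption; the protocol gives no figure. With 30% in one group and a mean score difference of d within-group SDs, R² = 0.21d²/(1 + 0.21d²). That gives 0.17 for d = 1 and 0.46 for d = 2, so 0.25 to 0.5 is a plausible range but not a documented one.

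**Step 4. Attenuation.** Step 3 holds the HR at 1.3 and counts only lost precision. As a limiting case, 200 data sets of 1,000 patients were simulated per scenario, with recovery depending only on the graded score, group differences of 1.5 to 2.5 SD and about 340 events. The unadjusted HR was 1.29 to 1.31. With the score added it was 0.98 to 1.01, with 1.5 to 2.4 times the variance. The null result is built into that set-up, and death is not modelled, so it shows a direction and does not predict a size.

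**Step 5. The self-interaction.** For a 0/1 exposure X, the subgroup variable is X and the product is X × X = X. The three columns are identical (rank 1), so no interaction can be estimated. Stratifying does not help: within VS, or within MCS, there is no VS vs MCS contrast.

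**The case against.** The strongest reply has five parts.

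- **The models do not name the exposure.** Primary analysis never writes VS/MCS into the five models and speaks of the influence of each predictor. This is true: the joint model is an inference. It is a sound one, because the primary question, the exposure definition, the unadjusted Model 1 and the plan to plot curves by exposure group all presuppose an exposure term.
- **A reader might infer that Models 4 and 5 cannot be fitted, or that a false null conclusion will follow.** The documents do not support either. VS/MCS is a diagnostic category, not a function of the total score, so the models can be fitted and estimate a legitimate conditional contrast. Models 1-3 are free of CRS-R total, all five are displayed together, and none is named as decisive. A drop at Model 4 would be visible, but could not be assigned to imaging or to CRS-R, because both enter at once.
- **The protocol has safeguards.** The DAG sentence warns against over-adjustment, and item 5 of Sensitivity analyses compares stepwise, full and reduced adjustment. These help in part. Neither removes CRS-R total from Models 4 and 5, where it is fixed by name, and the article does not define the reduced model.
- **A reader might infer that the MCS− vs MCS+ comparison has been dropped.** It has not. Study objectives prespecifies it, and the subgroup list is introduced as non-exhaustive.
- **A reader might extend the self-interaction fault to baseline CRS-R score as an effect modifier.** That term overlaps with the exposure but is not algebraically degenerate, so it is not the same error.

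The mismatch in Step 1 and the redundancy in Step 5 stand.

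**Conclusion.** Two faults hold on the text.

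First, no listed model gives the VS vs MCS effect with the adjustment that the primary question names. The models that include neuroimaging also condition on a score from the instrument that defines the exposure, so they answer a different question, with less precision and probable attenuation. The loss of precision is illustrative: 80% power at 544 events becomes about 68% at R² 0.25 and 51% at R² 0.5, with R² assumed and HR held at 1.3. How far the HR itself would shrink cannot be derived from the documents. If the diagnostic behaviours carry information beyond the total score, the shrinkage would be smaller.

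Second, the interaction of VS vs MCS with itself is not estimable. This is exact and rests on no assumption, but it affects only analyses that the protocol labels exploratory.

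The CRS-R total remains a proper predictor in the prediction model; the fault is confined to the exposure models.

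**What to change.** - For the VS vs MCS question, name as primary a model with age, sex, educational level, comorbidities, etiology, GCS at admission, time from injury and the neuroimaging indices, without CRS-R total. State VS/MCS explicitly as the exposure term.
- Keep the model with CRS-R total as a labelled secondary analysis of what the diagnostic label adds beyond the score. Keep CRS-R in the prediction model and the predictor analyses.
- In Subgroup and interaction analyses, delete VS vs MCS from the factors crossed with the exposure.
- Run the MCS− vs MCS+ comparison as a separate contrast within MCS, or as part of a three-level exposure. It should not take the deleted factor's place: MCS−/MCS+ exists only within MCS, so its product with the exposure is again the same variable and not estimable.

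The cost is wording in the model list and the subgroup list. No patients, visits or data items change, and enrollment is planned to start only in June 2026.

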### Multimodal prognostic prediction model construction

A multimodal prognostic prediction model will be constructed in three hierarchically nested stages: (1) a Clinical Model incorporating demographic and injury-related variables (age, sex, etiology, GCS at admission, time from injury to enrollment, and baseline CRS-R total score) selected via LASSO regression with 10-fold cross-validation; (2) a Neuroimaging-Augmented Model adding DTI-derived fractional anisotropy (corticospinal tract and corpus callosum) and resting-state fMRI default mode network connectivity to Stage 1; and (3) a Fully Integrated Multimodal Model further incorporating baseline serum biomarkers (NfL, GFAP, S100B). Model discrimination will be quantified by the C-index; incremental value across stages will be assessed using IDI and NRI (95% CIs via bootstrap resampling, 1,000 iterations). The final model will undergo bootstrap internal validation with optimism correction, and calibration will be evaluated using the Harrell calibration plot.

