### Variables

#### Primary and secondary outcome variables

The primary outcome variables of this study are as follows: (1) pDoC recovery, defined as emergence from MCS (eMCS), operationalized as achieving a CRS-R communication subscale score ≥2 (functional interactive communication) or a motor subscale score ≥6 (functional object use), confirmed on ≥2 standardized CRS-R assessments conducted ≥7 days apart and sustained for ≥4 consecutive weeks. This criterion applies uniformly to patients with a baseline diagnosis of VS or MCS. All recovery determinations will be adjudicated by the independent Endpoint Adjudication Committee; (2) all-cause mortality, defined as death from any cause at any point during the 5-year follow-up period (up to and including month 60). In the competing-risk analytical framework, all-cause mortality serves as the primary competing risk event for the consciousness recovery outcome. Patients who survive to the end of the 60-month follow-up without having achieved the consciousness recovery endpoint will be administratively right-censored at month 60; and (3) major cardiovascular events (MACE), encompassing myocardial infarction (defined in accordance with the Fourth Universal Definition of Myocardial Infarction, requiring elevated cardiac biomarkers in conjunction with clinical evidence of myocardial ischemia), hospitalization for heart failure (defined as inpatient admission requiring intravenous diuretics or inotropic support), and stroke (confirmed by neuroimaging [CT/MRI] with neurological deficits persisting for more than 24 h).

Secondary outcome variables include: (1) changes in functional status, assessed using the Glasgow Outcome Scale–Extended (GOS-E) and the Disability Rating Scale (DRS) (8, 9); (2) dynamic changes in biomarkers, including serum neurofilament light chain (NfL), glial fibrillary acidic protein (GFAP), S100 calcium-binding protein B (S100B), and other injury- and recovery-related biomarkers; (3) health-related quality of life, evaluated using the EQ-5D questionnaire, with caregiver proxy responses employed when direct patient assessment is not feasible; and (4) rehospitalization rate, documented by recording the frequency and causes of readmission, with particular attention to common complications such as infections, seizures, and respiratory events.

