#### Predictor variables and covariates

Primary prognostic predictor variables have been selected based on established clinical and biological plausibility for predicting consciousness recovery: (1) etiology of brain injury (TBI, hypoxic-ischaemic encephalopathy, cerebrovascular event, metabolic/toxic encephalopathy, other), given that neurobiological recovery trajectories differ substantially across aetiological subgroups; (2) injury severity at the acute phase (GCS score at hospital admission); (3) time from acute brain injury to study enrollment; (4) CRS-R subscale scores at baseline (auditory, visual, motor, oromotor/verbal, communication, and arousal subscales); and (5) neuroimaging characteristics (white matter integrity on DTI, functional connectivity on fMRI). Pre-injury lifestyle characteristics [smoking status, alcohol consumption, physical activity (assessed via caregiver proxy report using IPAQ) (11), and dietary habits] are retained as exploratory secondary covariates; their collection is hypothesis-generating and their role as determinants of post-injury recovery will be interpreted with appropriate caution given the reliance on caregiver proxy report.

Pre-specified adjustment covariates in all multivariable models include age, sex, educational level, and comorbidities (e.g., cardiovascular disease, diabetes mellitus, chronic kidney disease). It should be noted that injury severity (GCS at acute admission) and the interval from injury to enrollment are designated as primary prognostic predictor variables in this study (see above), rather than as confounders, given their established direct effects on consciousness recovery trajectories; they will therefore enter the analytical models as predictors of interest rather than as adjustment terms. Effect modifiers—including age stratum (< 50 years vs. ≥50 years), injury type (traumatic vs. non-traumatic), and baseline CRS-R score—will be formally evaluated through prespecified subgroup analyses and interaction testing.

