### Follow-up procedures

Follow-up assessments will employ a hybrid surveillance strategy combining in-person evaluations with remote monitoring. Core neurobehavioral and functional assessments (CRS-R, GOS-E, DRS, EQ-5D, SF-36, FIM, HADS, and Zarit Caregiver Burden Interview) will be conducted at bedside by certified assessors at baseline and at 3, 6, 12, 24, 36, 48, and 60 months (8 assessment timepoints in total, comprising 7 in-person follow-up visits). The Chinese validated CRS-R (7) will be used throughout. Assessors must complete standardized training—covering scoring, ≥10 supervised assessments, and ICC ≥ 0.85 reliability—before independent use. The same assessor will evaluate each participant at all timepoints when feasible; if replaced, inter-rater reliability will be verified against the prior assessor’s last two evaluations. Total and subscale scores will be recorded at each visit. eMCS is defined by subscale-specific behavioral thresholds (per Primary Outcome Variables), not a total score of 23/23, which reflects full neurological recovery rather than functional communication or object use. Neuroimaging investigations (MRI/DTI/fMRI) and serum biomarkers (NfL, S100B, GFAP, and other injury-related biomarkers) will be performed at baseline and at 6, 12, 24, 36, 48 and 60 months. Following the 6-month visit, remote follow-ups will be conducted by telephone interview supplemented by caregiver-reported outcomes at 3-month intervals between scheduled in-person visits, primarily capturing vital status, rehospitalization events, and major adverse events. Remote follow-ups will be administered by uniformly trained research coordinators using standardized scripts, with video calls employed as an adjunct to confirm the patient’s general condition. In-person outpatient visits will be conducted by neurologists and rehabilitation therapists.

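### The prediction model's clinical stage offers LASSO only the CRS-R total, although the six baseline subscales are named primary predictors and recovery is defined on two of them

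*Protocol article*

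**What the plan says.** All places are in the protocol article.

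- *Multimodal prognostic prediction model construction*: Stage 1 has six candidates: age, sex, etiology, admission GCS, "time from injury to enrollment, and baseline CRS-R total score) selected via LASSO regression with 10-fold cross-validation". Stage 2 adds "DTI-derived fractional anisotropy (corticospinal tract and corpus callosum) and resting-state fMRI default mode network connectivity to Stage 1", and Stage 3 adds three serum biomarkers. Discrimination is measured by the C-index, and "incremental value across stages will be assessed using IDI and NRI" with bootstrap intervals.
- *General principles and descriptive statistics*: this subsection is said to give the full construction procedure, so the candidate list is a stated choice and not a detail left for later.
- *Predictor variables and covariates*: among the primary prognostic predictors are "CRS-R subscale scores at baseline (auditory, visual, motor, oromotor/verbal, communication, and arousal subscales". The total is not named there.
- *Study objectives*: the second objective refers to CRS-R "subscale profiles, and neuroimaging indices as independent predictors of consciousness recovery and unfavorable outcomes".
- *Primary and secondary outcome variables*: recovery means "achieving a CRS-R communication subscale score ≥2 (functional interactive communication) or a motor subscale score ≥6 (functional object use", confirmed and sustained.
- *Follow-up procedures*: "eMCS is defined by subscale-specific behavioral thresholds (per Primary Outcome Variables), not a total score of 23/23". Subscale scores are recorded at every visit.
- *Primary analysis*: Models 4 and 5 use the CRS-R total, while the nested prognostic comparison uses the baseline subscales.

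**The concern.** A total gives every point on every subscale the same weight. LASSO can shrink or drop the total, but it cannot recover separate weights for subscales it is never offered. The two subscales on which recovery will be judged are thus available at baseline but enter only as part of a sum. Stage 1 has no VS/MCS term either, so the total is its only baseline measure of consciousness, and Stages 2 and 3 are built on it.

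Two things could follow. The bedside model could discriminate less well than the collected data permit. And an imaging index that tracks the lost information could be credited with some of it; corticospinal-tract FA, as a correlate of the motor subscale, is a plausible candidate. Both depend on how recovery relates to the subscales, on which the documents give no data.

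**Working it through.** **1. The plan's own figures.** An 8% annual rate gives 1 − 0.92^5 = 0.341, matching the stated 34%. The Schoenfeld formula gives (1.960 + 0.842)² / (0.3 × 0.7 × (ln 1.3)²) = 543 events, against 544 stated. That is a requirement, not the expected count. For model size I use the expected recoveries: 1,000 × 0.34 = 340, or 340 × 0.85 = 289 after the planned 15% loss.

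**2. Is there room for the subscales?** Count etiology (five categories) as four parameters.

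| Stage | Parameters, total | Parameters, subscales | Events per parameter, subscales (289 / 340) |
|---|---|---|---|
| 1 | 4 + 5 = 9 | 4 + 10 = 14 | 20.6 / 24.3 |
| 2 (+3 imaging) | 12 | 17 | 17.0 / 20.0 |
| 3 (+3 biomarkers) | 15 | 20 | 14.4 / 17.0 |

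With the total, Stage 3 has 19.3 / 22.7. Event numbers do not force the use of the total.

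**3. How much could be lost?** The documents give no subscale effects or correlations, so everything in this step is assumed. Set-up, with 100,000 simulated patients per scenario:

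- Six ordinal subscales with baseline maxima 4, 5, 5, 3, 1, 3. Motor stops at 5 and communication at 1 because patients already in eMCS are ineligible. The full-scale maxima 4 + 5 + 6 + 3 + 2 + 3 add to the protocol's 23.
- Latent correlation between subscales of 0.3 or 0.6.
- A logistic outcome whose linear predictor has SD 1, giving 34-35% recovery.
- An imaging marker correlated 0.3 or 0.6 with motor, with no effect of its own.

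Each outcome was fitted with the total and with the six subscales, with and without the marker. Loss = C(subscales) − C(total). False gain = C or IDI added by the marker over the total.

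| What drives recovery | C, total | C, subscales | Loss in C | False gain in C | False gain in IDI |
|---|---|---|---|---|---|
| Equal weight per point | 0.747-0.751 | 0.747-0.751 | about 0 | about 0 | 0 |
| Equal weight per SD | 0.742-0.750 | 0.747-0.753 | 0.002-0.005 | ≤ 0.0004 | ≤ 0.0001 |
| Motor and communication double | 0.736-0.745 | 0.749-0.751 | 0.006-0.013 | ≤ 0.0006 | ≤ 0.0002 |
| Motor and communication only | 0.679-0.715 | 0.749-0.751 | 0.036-0.071 | 0.001-0.007 | 0.0003-0.006 |

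With the subscales in the base model, the false gain is nil to three decimals in every row.

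**4. At the planned size.** Simulations with N = 1,000 and latent correlations of 0.3-0.7 give apparent losses of about 0.01-0.02 with double weights and 0.03-0.06 when only the two subscales matter, so the ranges over both sets are 0.01-0.02 and 0.03-0.07. With equal weights the apparent gap of 0.004-0.009 is all optimism.

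**Limits.** The illustration is logistic. It leaves out the other clinical candidates, the LASSO step and death as a competing event. It shows direction and order of size, not a forecast.

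**The case against.** The strongest defence is that this is a modelling choice. The prediction model is introduced as a separate, dedicated model, and nothing obliges its candidates to match the list of primary predictors. Models 4 and 5 also use the total, and one score is simpler at the bedside. The total already contains the motor and communication points, and the eligibility rules narrow both ranges at baseline. If all six subscales matter about equally, the total loses almost nothing and the extra terms add only estimation noise. All of this stands, and it limits the claim to a conditional one.

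The nested comparison in *Primary analysis* is a partial answer: it enters subscales and imaging together, so imaging effects adjusted for the subscales will be seen. But no C-index, IDI or NRI increment is planned from it. The sensitivity analysis on covariate adjustment concerns effect estimates, not the prediction stages.

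A reader might infer more: that the clinical benchmark is in fact weakened and that imaging will be credited with bedside information. The documents do not support that. It needs subscales that predict beyond their sum and imaging that tracks the remainder, and neither is shown. Simulation can make it look alarming: when only motor and communication matter, a null marker correlated 0.3-0.5 with motor reaches 5% significance on a likelihood-ratio test over the total in about 8-37% of studies. That is the least favourable scenario, although the protocol names all six subscales as predictors, and the plan does not use that test. Nor is the third objective judged only by the increment; it is to develop and validate a model.

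**Conclusion.** The mismatch is real: the subscales are named predictors in the objectives, the predictor list and the nested comparison, while the prediction model fixes the total without giving a reason. Its consequence is a risk of nil to modest size. The steadier cost is accuracy of the clinical model: about 0 in C with equal weights, 0.01-0.02 with motor and communication at double weight, and 0.03-0.07 if only those two matter. Inflation of the imaging increment is secondary, at most about 0.007 in C and 0.006 in IDI in that last scenario and near nil otherwise. These figures rest on assumed correlations and weights. The change is worth making because it is cheap and gives a fairer benchmark, not because bias has been demonstrated.

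**What to change.** In Stage 1 of the prediction model, replace the baseline CRS-R total with the six baseline subscale scores as LASSO candidates. Do not offer both, since the total is their sum. Carry the selected clinical terms into Stages 2 and 3, so that imaging and biomarkers are measured against the full bedside assessment. Keep the total-score version as a simpler secondary model.

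At minimum, if the total stays in the main model, give the reason and repeat the C-index, IDI and NRI increments against a subscale-based clinical model.

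Cost: a small change of wording and no new data collection. There are five more candidate terms, which the planned penalty and optimism correction are suited to handle, and a slightly less simple bedside model.
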